**Post discharge follow-up phone calls Protocol**

**Clinical Trials Protocol: MSHCANADA-CSCB**

**Introduction**

Currently, discharge from hospital in many institutions is a confusing process for patients filled with uncertainty and potential for harm. For instance, 1 in 5 discharges results in a post discharge adverse event, many of which are related to medication errors.^1,2^ These may lead to serious harm and possibly require readmission to hospital. Prior research suggests conducting post discharge follow up phone calls may improve patient satisfaction, reduce unnecessary hospital visits, and improve adherence to medications and discharge care plans.^3^ However, there are few studies focused on general medicine patients and most were of small sample size of low methodological quality. We propose a randomized controlled trial to determine the effect of post discharge phone calls on patient outcomes in general medical patients.

**Hypothesis**

A post discharge follow up phone call to general medical patients discharged home will improve Care Transition Measure scores, adherence to treatment plan (including medication) and patient satisfaction, and decrease medication error and subsequent hospital utilization including readmission and emergency department visits in the Local Health Integration Network.

**Significance**

The transition from hospital to home is a critical period during which significant harm or avoidable resource utilization can result from lack of supports and poor understanding of discharge plans. Telephone follow-up calls after discharge has been studied in small single-center trials and as a part of a coordinated, multi-layered discharge process but its direct effectiveness is not known. Understanding the impact of this simple intervention on patient outcomes is an important step towards improving patients’ discharge from hospital.

**Methods**

Setting

Mount Sinai Hospital, an academic medical centre with general medicine inpatient units.

Patients

All patients admitted to a general internal medicine ward who survive to hospital discharge home.

Exclusion criteria: Patients who do not have a telephone, patients discharged to a facility (rehabilitation, nursing, other acute care facility), patients who decline to participate.

Study design:

Cluster randomized control trial in a teaching hospital. Clinical teaching unit (CTU) “teams” of patients will be randomized to receive either routine care (no telephone follow up) or intervention (telephone follow up within 72 hrs of discharge). All patients will be followed 30 days after discharge and contacted to collect survey outcome data. Clinical outcomes data will be collected from hospital database.

Survey Design:

Intervention group will receive a phone call within 72 hours after discharge addressing the following domains:

- Patient status since discharge
- Patient’s understanding of discharge instructions
- Patient’s understanding of changes in his/her medications
- Any follow up visits to family practitioner or other specialists
- Any concerns or questions outstanding

All patients will be contacted at 30-days post-discharge to complete a survey regarding outcomes. The survey will contain the Care Transitions Measure-3 (CTM-3), a validated tool to evaluate patients’ perception on coordination of hospital discharge care in addition to questions pertaining to hospital utilization, and rates of adherence to treatment plans and follow up. Follow up surveys may be conducted up to 90 days post discharge.

Callers will follow a standardized script. Patients will be contacted at least five times (unless respondent refuses to participate) to complete the intervention and follow-up survey. Attempts must be made on different days and at different times of the day.

Data Collection

| **Variable** | **Measurement** | **Variable Type** |
| --- | --- | --- |
| *Patient Demographics*  Age  Sex  Admitting diagnosis  Most responsible diagnosis  Family physician  Mean length of stay | Hospital Chart | Continuous  Binary  Categorical  Categorical  Binary  Continuous |

Primary Outcome

Change of 5-points on the Care Transition Measure-3 score (survey)

Secondary Outcomes

30-day Hospital Readmission (TC-LHIN data)

ED visits within 30 days or weeks (TC-LHIN data)

Patient satisfaction (survey)

Adherence to treatment plan (survey)

Rates of follow up with PCP/outpatient providers (survey)

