**Statistical Analysis**

Sample size justification

A previous study using the CTM-3 in a similar patient population found a mean of 80.3% with a standard deviation of 19.6.^4^ We determined that a 7-point absolute difference in CTM-3 scores would be clinically relevant to physicians and hospital administrators. With an alpha-error of 0.05 (2-sided) and a beta-error of 0.20 (1-sided), the unadjusted total sample needed to detect a 7-point difference in CTM-3 scores was 95 in each arm. Assuming a 50% response rate of patients completing the post-discharge survey, we calculated an adjusted sample size of 190 in each arm, or 380 patients in total. Given that over an average month, 254 patients are discharged from the GIM service at our hospital and assuming a conservative historical trend of 80% of patients returning home and a 50% participation rate, we elected to conduct the study over a 4-month period.

Descriptive analyses will be used to summarize results (e.g., means, medians, and standard deviations). Continuous variables will be compared using Mann-Whitney test and categorical variables with Fisher’s exact test or Chi-square.

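### The primary outcome is worded as a 5-point change on CTM-3, but CTM-3 is measured once and the trial is sized on a 7-point difference between arms

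*Protocol*

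**What the plan says.** The Protocol, Methods (Primary Outcome), gives the whole definition in one line: "Change of 5-points on the Care Transition Measure-3 score (survey". It names no starting point for the change, no comparator and no summary measure.

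Methods (Survey Design) says when and how the score is obtained: "All patients will be contacted at 30-days post-discharge to complete a survey regarding outcomes", and "The survey will contain the Care Transitions Measure-3 (CTM-3), a validated tool to evaluate patients’ perception on coordination of hospital discharge care". Timing is relaxed by one further sentence: "Follow up surveys may be conducted up to 90 days post discharge".

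Statistical Analysis (Sample size justification) works with a different number: "We determined that a 7-point absolute difference in CTM-3 scores would be clinically relevant to physicians and hospital administrators". It takes its variability from a previous study that "found a mean of 80.3% with a standard deviation of 19.6", sets the error rates ("With an alpha-error of 0.05 (2-sided) and a beta-error of 0.20 (1-sided") and concludes that "the unadjusted total sample needed to detect a 7-point difference in CTM-3 scores was 95 in each arm". The same section plans to compare continuous variables by the Mann-Whitney test.

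**The concern.** A primary outcome should say what is measured on each patient, when, and how the arms are compared. This one gives a number of points and the word change. With a single assessment there is nothing for a patient's score to change from, so the wording does not match the data to be collected.

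The 5 points are a second problem. The sample size section calls 7 points clinically relevant, and nothing in the Protocol explains why the outcome carries a smaller figure. If the trial observed a difference of 5 to 6 points, one part of the Protocol would support calling it relevant and another would not. The statement of power also depends heavily on which figure is taken as the target.

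**Working it through.** **Is a change measured anywhere?** Each place where an earlier CTM-3 score could sit was checked.

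- The data collection table in Methods lists demographics, diagnoses, family physician and length of stay. It has no CTM-3.
- The call within 72 hours goes to the intervention arm only, and CTM-3 is not among its five listed domains.
- The allowance to 90 days permits a late survey. It does not describe a second one.
- The Protocol describes CTM-3 as a rating of how discharge care was coordinated, so a score before discharge would have little meaning.

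There is one score per patient. A within-patient change, or a responder defined by one, cannot be derived.

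**What comparison does the rest of the Protocol imply?** The Hypothesis section expects the call to improve CTM-3 scores. The sample size section uses an absolute difference and the SD of a single score, not of a change. The planned tests are two-group tests. All of this points to comparing the survey score between arms, which the planned data allow.

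**Inputs** (Protocol, Statistical Analysis, except the 5 points, which come from Methods): SD 19.6; two-sided alpha 0.05 (z = 1.960); power 80% (z = 0.842); difference d = 7 or 5; 95 completers per arm; 50% survey response.

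**The plan's own figure.** n per arm = 2 × (1.960 + 0.842)² × 19.6² / d².

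- For d = 7: 2 × 7.85 × 384.16 / 49 = 123.1, so 124 per arm. The stated 95 is not reproduced. With a one-sided alpha of 0.05 (z = 1.645) the formula gives 97, close to 95, but the Protocol states a two-sided alpha.
- The inflation step is reproduced: 95 / 0.50 = 190 per arm, 380 in total.

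**The same formula for 5 points.** 2 × 7.85 × 384.16 / 25 = 241.2, so 242 per arm.

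**Power at 95 completers per arm.** The standard error of the difference is 19.6 × √(2/95) = 2.844. Power is approximately Φ(d / 2.844 − 1.960).

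| Target difference | d / SE − 1.960 | Power at 95 per arm | Completers per arm for 80% | Enrolled in total at 50% response |
| --- | --- | --- | --- | --- |
| 7 points | 0.501 | 69% | 124 | 496 |
| 5 points | −0.202 | 42% | 242 | 968 |

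**Where the two thresholds would bite.** With 95 per arm, the smallest observed difference significant at the two-sided 5% level is about 1.960 × 2.844 = 5.6 points. An observed 6 points would be significant, above 5 and below 7.

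These are normal-approximation figures for a difference in means, with no allowance for cluster randomisation. Dividing by 0.955, the efficiency of the Mann-Whitney test relative to the t-test under normality, raises 124 to about 130 and 242 to about 254.

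**The case against.** The strongest reply is that the intention is clear enough. Read with the Hypothesis and Statistical Analysis sections, change is loose wording for a difference between arms, and that comparison can be made. This stands. A reader might infer that the primary endpoint cannot be computed at all; the documents do not support that. Only the literal reading fails.

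A reader might also infer that the sponsor could choose the threshold for a positive result after seeing the data. That is not supported either. On the analysis described, a positive result comes from a two-sided test at 0.05, and neither 5 nor 7 points is a decision rule for it. The two numbers bear on clinical relevance and on stated power. They would affect the test only under a responder analysis, which the Protocol does not describe.

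Third, the 242 completers per arm and 968 patients describe a trial that this Protocol does not plan, since it is explicitly sized on 7. That is right. They show how far apart the two figures are; they are not a shortfall against a commitment. Nor should the 42% be read as if 7 points were adequately powered: on the stated inputs 95 per arm falls short there too, for a reason separate from the 5-versus-7 conflict.

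Finally, a statistical analysis plan that is not shown may define the outcome properly. It would still not remove the contradiction between two sections of the Protocol.

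**Conclusion.** The point holds as an internal inconsistency in the definition of the primary outcome. The wording implies a change that is not measured, and its 5 points disagree with the 7 points used for sizing. The intended between-arm comparison remains computable and the significance test is unaffected. What is unsettled is which difference counts as clinically relevant and what power the trial can claim: about 69% for 7 points and 42% for 5 points at 95 completers per arm.

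The power figures assume SD 19.6 in both arms, approximate normality and independent patients. The last two are favourable assumptions. The quoted mean plus one SD is 80.3 + 19.6 = 99.9, so on a scale taken to end at 100 the scores are likely to be skewed. The teams are also randomised as clusters. The contradiction itself rests on none of these assumptions. It should be corrected because it sits in the primary outcome.

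**What to change.** 1. In Methods (Primary Outcome), define the outcome as the CTM-3 score at the post-discharge survey, compared between arms, and delete the 5-point change. State the scale (taken here as 0 to 100, because the Protocol quotes its mean as a percentage) and the timing, including how surveys completed between 30 and 90 days are treated.
2. State one target difference and use it in both sections. Seven points is the one used for sizing, although the Protocol asserts its relevance without deriving it, so a sentence of justification would help.
3. Report the mean difference with a 95% CI and say how it relates to the Mann-Whitney test in Statistical Analysis, which does not test a difference in means. Either name one as primary, or make the estimate and test correspond.
4. Restate the power for the difference kept: at 95 completers per arm, about 69% for 7 points or about 42% for 5, before any allowance for clustering.

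The cost is a wording change and a less favourable stated power. No extra data are needed if the planned size is kept. Restoring 80% power would be a separate decision, needing about 496 enrolled for 7 points or 968 for 5, against 380 planned, again before clustering.

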**Statistical Analysis**

Sample size justification

A previous study using the CTM-3 in a similar patient population found a mean of 80.3% with a standard deviation of 19.6.^4^ We determined that a 7-point absolute difference in CTM-3 scores would be clinically relevant to physicians and hospital administrators. With an alpha-error of 0.05 (2-sided) and a beta-error of 0.20 (1-sided), the unadjusted total sample needed to detect a 7-point difference in CTM-3 scores was 95 in each arm. Assuming a 50% response rate of patients completing the post-discharge survey, we calculated an adjusted sample size of 190 in each arm, or 380 patients in total. Given that over an average month, 254 patients are discharged from the GIM service at our hospital and assuming a conservative historical trend of 80% of patients returning home and a 50% participation rate, we elected to conduct the study over a 4-month period.

Descriptive analyses will be used to summarize results (e.g., means, medians, and standard deviations). Continuous variables will be compared using Mann-Whitney test and categorical variables with Fisher’s exact test or Chi-square.

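### The stated 95 completers per arm do not give 80% power for a 7-point CTM-3 difference with SD 19.6: those inputs need about 124, and 95 gives about 69%

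*Protocol*

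**What the plan says.** The justification is one paragraph in the Protocol, Statistical Analysis, under the sample size heading. It takes the variability from a previous study that "found a mean of 80.3% with a standard deviation of 19.6". The target is set next: "We determined that a 7-point absolute difference in CTM-3 scores would be clinically relevant". The error rates are given as "With an alpha-error of 0.05 (2-sided") and "a beta-error of 0.20 (1-sided"). From these it states that "the unadjusted total sample needed to detect a 7-point difference in CTM-3 scores was 95 in each arm".

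The figure is then carried forward. "Assuming a 50% response rate of patients completing the post-discharge survey", the Protocol continues, "we calculated an adjusted sample size of 190 in each arm, or 380 patients in total". Finally, from 254 discharges a month, 80% going home and 50% participating, it says "we elected to conduct the study over a 4-month period".

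The paragraph states no second SD, no baseline adjustment, no unequal allocation and no allowance for clustering.

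**The concern.** The paragraph supplies every input of a standard two-mean calculation, so its result can be checked directly, and 95 is too small. With a standardized difference of 7/19.6 = 0.357, a two-sided 5% test at 80% power needs well over 100 per arm.

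This is the only sample size justification in the Protocol, and it concerns the primary outcome. Anyone relying on it, such as an ethics board, the hospital office asked for funding or a later reader, would take the trial to have 80% power for the difference that the Protocol itself calls clinically relevant. If the true power is nearer 69%, a non-significant result would be over-read as evidence against a 7-point effect.

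**Working it through.** **Inputs** (all from the Protocol, Statistical Analysis): SD σ = 19.6; difference δ = 7; two-sided alpha 0.05, so z = 1.960; beta 0.20, so z = 0.842; equal arms; 50% survey response.

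**Step 1. Attempt to reproduce 95 from the stated inputs.**

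n per arm = 2 (z₁₋α/₂ + z₁₋β)² σ² / δ²

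= 2 × (1.960 + 0.842)² × 19.6² / 7²

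= 2 × 7.849 × 384.16 / 49 = 123.07, so **124**.

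Solving with the t distribution gives 124.04. Strict rounding up would make that 125, but power at 124 is already 79.99%. The stated 95 is 29 short of 124, or 23% too low, which is far more than rounding or the choice of formula can explain.

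**Step 2. Power at 95 per arm for 7 points.**

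Standard error of the difference = 19.6 × √(2/95) = 2.844.

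δ/SE = 7 / 2.844 = 2.461.

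Power ≈ Φ(2.461 − 1.960) = Φ(0.501) = **69.2%**; t-based **68.8%**. The type II risk is therefore about 31%.

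**Step 3. Difference detectable with 80% power at 95 per arm.**

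δ = (1.960 + 0.842) × 2.844 = 7.97; t-based 8.01. So about **8.0 points**.

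**Step 4. Which change of input would give 95?**

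| Change to one stated input | n per arm | What the text says |
| --- | --- | --- |
| Difference of 8 points | 94.2, so 95 (t: 95.2) | 7 points |
| One-sided alpha 0.05 | 96.9, so 97 (t: 97.6) | two-sided |
| Power 70% | 97 | beta 0.20 |
| SD about 17.2 (t: 17.1) | 95 | 19.6 |
| 2:1 allocation | 93 in the smaller arm | equal arms |

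An 8-point difference fits best, but the document does not show which input was used. Every route contradicts something that the paragraph states.

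**Step 5. What carries through.**

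The response step is arithmetically right: 95 / 0.5 = 190 per arm and 2 × 190 = 380. It passes the error on. From the corrected start: 124 / 0.5 = 248 per arm, **496 in total**, which is 116 more than 380.

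Accrual as projected: 254 × 0.8 × 0.5 = 101.6 participants a month, so 406 in four months. That covers 380 but not 496, which would take 496 / 101.6 = 4.9 months. If half of the 406 respond, there are 101 to 102 completers per arm, with t-based power for 7 points of 71% to 72%.

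**Step 6. Direction of what is left out.**

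Steps 1 to 5 assume individually randomized patients and a comparison of means. The Methods section randomizes clinical teaching unit teams, so any positive within-team correlation raises the requirement. The planned Mann-Whitney test would, under normality, need about 124 × π/3 = 130 per arm. On both counts 124 is a lower figure.

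**The case against.** The arithmetic itself has no good defence: nothing else in the Protocol supplies an input that would rescue 95, and a separate analysis plan could not make this sentence correct. The serious objections concern the consequences and the remedy.

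- **Duration.** The paragraph uses 50% twice, once as a survey response rate and once as a participation rate. If both describe the same loss, the 406 would be completers, about 203 per arm. Power for 7 points would then be about 95% under individual randomization, and four months would be enough. The more natural reading is that 406 are enrolled: the figure answers a target of 380 that already allows for non-response, and the Methods section excludes patients who decline. Still, the text does not settle it, so the need for about 4.9 months depends on that reading. The 95, 190 and 380 are wrong on either reading.
- **Replacement figures.** Putting in 124, 248 and 496 without comment would install another number that ignores team randomization and the Mann-Whitney test. This stands: those figures can only be given as minimums. The Protocol states neither the number of teams nor an intraclass correlation, so no final figure can be derived from it.
- **Target.** The primary outcome is worded as a 5-point change, whereas the calculation uses 7. At 5 points the same inputs need 242 per arm. This is a separate matter, but it should be settled before any recalculation.
- **Source of the error.** An input may be misprinted rather than the result. That is possible, and the sponsor should say which. The paragraph as written is wrong in either case.

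**Conclusion.** The concern holds. On the Protocol's own inputs the requirement is about 124 completers per arm, not 95. With 95 the power for 7 points is about 69%, and 80% power is reached only at about 8.0 points. The 190 and 380 inherit the error.

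These results rest on the stated SD of 19.6, equal arms, individual randomization and a comparison of means. The last two favour the plan, so the real shortfall is likely to be larger. The consequence for duration also assumes that the 406 projected participants are enrolled patients, of whom half complete the survey. This should be corrected, because it misstates the power for the primary outcome.

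**What to change.** Correct the sample size paragraph, and have the sponsor state which inputs produced 95.

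**If size and duration stay as they are:** restate the power. Suggested wording: *With 95 survey completers per arm, an SD of 19.6 and a two-sided alpha of 0.05, power is about 69% for a 7-point difference and 80% for an 8.0-point difference, assuming individual randomization and a comparison of means.* This costs the rewording of one paragraph and a less favourable power statement. It needs no extra patients.

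**If 80% power for 7 points is to be kept:** replace 95, 190 and 380 with at least 124, 248 and 496. State that these are minimums before any allowance for team randomization or the Mann-Whitney test, and change four months to about five if participation and survey response are separate losses. This is not just rewording: it adds 116 patients and about a month of accrual, with a half-time coordinator for whom funding has only been applied for.

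Under either option, say whether the two 50% rates are distinct.

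### The trial randomizes teams but is sized as if patients were randomized, so the stated 80% power makes no allowance for clustering

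*Protocol*

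**What the plan says.** Under Study design, the Methods section describes a "Cluster randomized control trial in a teaching hospital" and makes the team the unit of allocation: "Clinical teaching unit (CTU) “teams” of patients will be randomized to receive either routine care (no telephone follow up) or intervention".

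The sample size justification under Statistical Analysis draws on an earlier study that "found a mean of 80.3% with a standard deviation of 19.6". It takes 7 CTM-3 points as the difference to detect, sets two-sided alpha at 0.05 and beta at 0.20, and concludes that "the unadjusted total sample needed to detect a 7-point difference in CTM-3 scores was 95 in each arm". One adjustment follows: "Assuming a 50% response rate of patients completing the post-discharge survey, we calculated an adjusted sample size of 190 in each arm", which makes 380 patients in all. The four-month duration is then justified from 254 discharges a month, "assuming a conservative historical trend of 80% of patients returning home and a 50% participation rate".

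The protocol nowhere states an ICC, a number of teams, a team size or a design effect. It also does not say whether each team is allocated once or again in successive periods.

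**The concern.** Patients discharged by one team share staff and discharge practice, and the CTM-3 asks how patients perceived the coordination of their discharge. Under Budget Justification, members of the care teams also make the intervention calls. Scores within a team can therefore be expected to be correlated. If they are, 95 completers carry less information than 95 independent patients, and a valid comparison also has few degrees of freedom when few teams are randomized.

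This is not something left to a later analysis plan. The protocol carries the calculation through, calls the result adjusted, and sets enrolment and duration from it. If the 80% stands unqualified, a null result may be read as evidence that the call does not work, when the trial may have had much less power to show a 7-point difference.

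**Working it through.** **Inputs from the protocol.** Difference d = 7 points, SD = 19.6, two-sided alpha 0.05, power 80%, equal arms, 95 completers per arm, 50% response. The Methods section names 5 points for the primary outcome; that is a separate discrepancy, and 7 is used here because the calculation uses it.

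**Assumed, because the protocol is silent.** ICC 0.01 to 0.05; 4 or 8 equal-sized teams in total, that is k = 2 or 4 per arm.

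**Step 1: the plan's own figures.** The response step reproduces: 95 / 0.5 = 190 per arm, 380 in total. The 95 does not:

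- n per arm = 2 × [19.6 × (1.960 + 0.842) / 7]² = 123.1, so 124.
- With one-sided alpha (1.645 in place of 1.960) the formula gives 96.9, so 97. That is close to 95, but the protocol says two-sided.

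**Step 2: power before any clustering.** With 95 per arm, SE = 19.6 × √(2/95) = 2.844 and 7 / 2.844 = 2.461. Power = Φ(2.461 − 1.960) = 69%. With 124 per arm it is 80%. About 11 points are therefore lost to the base figure alone.

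**Step 3: adding the design effect.** Completers per team m = n / k; design effect DE = 1 + (m − 1) × ICC; effective n = n / DE. Power is computed from the effective n with a normal reference, and with a noncentral t on 2(k − 1) degrees of freedom.

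Example, 95 per arm, 8 teams, ICC 0.01: m = 23.75; DE = 1 + 22.75 × 0.01 = 1.23; effective n = 77; SE = 3.151; 7 / 3.151 = 2.222; power = Φ(2.222 − 1.960) = 60%.

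| Completers per arm | Teams in total | ICC | DE | Effective n per arm | Power, normal | Power, t |
|---|---|---|---|---|---|---|
| 95 | 8 | 0 | 1.00 | 95 | 69% | 54% (6 df) |
| 95 | 8 | 0.01 | 1.23 | 77 | 60% | 46% |
| 95 | 8 | 0.05 | 2.14 | 44 | 39% | 30% |
| 95 | 4 | 0 | 1.00 | 95 | 69% | 29% (2 df) |
| 95 | 4 | 0.01 | 1.47 | 65 | 53% | 22% |
| 95 | 4 | 0.05 | 3.33 | 29 | 27% | 13% |
| 124 | 8 | 0.01 | 1.30 | 95 | 69% | 54% |
| 124 | 8 | 0.05 | 2.50 | 50 | 43% | 32% |
| 124 | 4 | 0.01 | 1.61 | 77 | 60% | 25% |
| 124 | 4 | 0.05 | 4.05 | 31 | 29% | 14% |

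The 124 rows isolate clustering, because unclustered power there is 80%.

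**Step 4: would more patients in the same teams help?** Doubling from 95 to 190 completers per arm, normal reference:

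- 8 teams, ICC 0.01: 60% to 82% (46% to 67% on 6 df).
- 8 teams, ICC 0.05: 39% to 48%.
- 4 teams, ICC 0.05: 27% to 31%.

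With k teams per arm fixed, 80% power on the normal reference needs 124 × (1 − ICC) / (1 − 124 × ICC / k) completers per arm. For k = 4 and ICC 0.01 this is 122.76 / 0.69, so 178, or 356 enrolled per arm at 50% response. That compares with 190 per arm planned and 254 × 0.80 × 0.50 × 4 = 406 patients expected in total. For k = 4 and ICC 0.05 the denominator is 1 − 1.55, which is negative: no number of patients suffices.

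**The case against.** The omission is plain on the page, so the case on the other side concerns its size and cause.

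First, a reader might infer that the missing design effect explains the whole gap below 80%. It does not. Power is already 69% at ICC = 0 because 95 does not follow from the stated inputs. With 8 teams at ICC 0.01, clustering costs about 9 points (69% to 60%), not 20. This objection stands, and it is why the 69% baseline and the 124 rows are shown.

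Second, neither the ICC nor the number of teams comes from the protocol. With 16 teams and ICC 0.005, DE is 1.05 and power is 67%, only 2 points below the unclustered value. Repeated allocation over the four months could also raise the number of randomized units. This stands too: the size of the loss is illustrative. The omission itself does not depend on it.

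Third, a reader might take 22%–13% as this trial's power. Those figures assume 4 teams and a cluster-level t reference, whereas the protocol plans a patient-level Mann-Whitney test for continuous variables. Much of that drop comes from having 2 degrees of freedom: power there is 29% even at ICC = 0. The figures describe a valid cluster analysis under that assumed team count; they are not the loss from the design effect alone.

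Fourth, it is tempting to say that extra patients in the same teams achieve little. That is too general: at ICC 0.01 with 8 teams, doubling the completers restores 80% on the normal reference. It holds only for an ICC near 0.05 or for very few teams.

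**Conclusion.** The point holds as an error in the protocol as written. The design is clustered, the sample size is not, and the stated 80% therefore makes no allowance for the way patients are allocated. No particular achieved power can be asserted, because the ICC and the number of teams are unknown.

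Two causes must be kept apart. The base figure of 95 costs about 11 points on the protocol's own two-sided inputs, with no assumption about clustering. Any positive ICC costs more. For ICC 0.01 to 0.05, correcting the base alone would still leave the trial well below 80% with 4 or 8 teams. These figures assume equal team sizes and an analysis that accounts for clustering; the patient-level tests the protocol names are a related but separate matter.

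This should be corrected before the power statement is relied on: the mismatch is clear and correcting the statement is cheap.

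**What to change.** Rewrite the sample size justification under Statistical Analysis as follows:

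- State how many teams, or team-periods if allocation is repeated, are randomized to each arm, and the expected completers per unit.
- Give an assumed ICC as a small range with its justification, and the design effect 1 + (m − 1) × ICC.
- Recalculate the base from the stated two-sided inputs (about 124 completers per arm) and apply the design effect to that, not to 95. Non-response inflation comes after.
- In place of the unqualified 80%, give the power for 7 points, or the detectable difference, for the planned completers on cluster degrees of freedom across the ICC range.
- Commit to reporting the observed ICC with the results.

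The cost is one paragraph and a lower stated power, with no extra patients. This makes the power statement honest but does not restore the power. If the sponsor wants 80%, the number of randomized units has to be considered along with the number of patients, because at the upper end of the ICC range more patients in the same 4 or 8 teams cannot reach it.

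### Teams are randomized but the named tests treat patients as independent; if outcomes correlate within teams, type I error exceeds the stated 5%

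*Protocol*

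**What the plan says.** Under Study design, the Methods section of the protocol labels the trial: "Cluster randomized control trial in a teaching hospital". The unit of allocation follows: "Clinical teaching unit (CTU) “teams” of patients will be randomized to receive either routine care" or the telephone intervention.

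The Statistical Analysis section then fixes the comparisons: "Continuous variables will be compared using Mann-Whitney test and categorical variables with" Fisher's exact or chi-square tests. The error rates are also fixed there: "With an alpha-error of 0.05 (2-sided) and a beta-error of 0.20 (1-sided").

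The sample size is counted in patients: 95 per arm, raised to 190 per arm (380 in total) for a 50% survey response. That is the only adjustment. The protocol contains no random team effect, GEE, team-level summary, clustered or permutation version of the tests, ICC or design effect. The number of teams is not stated.

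**The concern.** In their standard form, the three named tests assume independent observations. Patients of one team share physicians and discharge practice, and CTM-3 asks patients how well their discharge was coordinated, so correlation within teams is plausible. The Budget Justification section adds a second possible source: care-team members make the intervention calls, so caller effects may also follow teams.

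When teams are allocated, chance differences between the teams in the two arms add to the variance of the between-arm comparison. A patient-level test leaves that component out, so its standard error is too small. This affects CTM-3 and every secondary comparison: readmission, ED visits, satisfaction, adherence and follow-up visits. A finding declared significant at 5% could reflect which teams happened to fall in which arm.

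This is not a detail left for a statistical analysis plan. The protocol names specific tests, and they do not fit the design it describes.

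**Working it through.** **Inputs from the protocol (Statistical Analysis).** Two-sided alpha 0.05; power 80%; difference 7 points ("We determined that a 7-point absolute difference in CTM-3 scores would be clinically relevant"); SD 19.6 ("found a mean of 80.3% with a standard deviation of 19.6"); 95 evaluable patients per arm ("the unadjusted total sample needed to detect a 7-point difference in CTM-3 scores was 95 in each arm"), so 190 completers.

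**Assumed, because the protocol does not give them.** Number of teams (4, 8 or 16 in total, split equally between arms) and ICC (0.001 to 0.05).

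**Step 1: the plan's own figure.** n per arm = 2 × (SD × (z_alpha + z_beta) / difference)².
- Two-sided: 2 × (19.6 × (1.960 + 0.842) / 7)² = 123.07, so 124 per arm, not 95. With 95 per arm, two-sided power is 69.2%.
- One-sided alpha of 0.05: 96.94, so 97 per arm, close to 95.

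This mismatch is a separate matter and does not drive the present point. What matters here is that neither 95 nor 124 contains a design effect: the calculation treats patients as independent.

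**Step 2: type I error of a patient-level test.** With m completers per team, the design effect is DE = 1 + (m − 1) × ICC. A test that ignores clustering, run at nominal 5%, has true two-sided error 2 × (1 − Φ(1.96 / √DE)).

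Worked example, 4 teams and ICC 0.01: m = 190 / 4 = 47.5; DE = 1 + 46.5 × 0.01 = 1.465; 1.96 / √1.465 = 1.62; error = 10.5%.

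| Teams in total (m) | ICC 0.001 | 0.005 | 0.01 | 0.02 | 0.05 |
|---|---|---|---|---|---|
| 4 (47.5) | 5.5% | 7.7% | 10.5% | 15.8% | 28.2% |
| 8 (23.75) | 5.3% | 6.3% | 7.7% | 10.4% | 18.0% |
| 16 (11.9) | 5.1% | 5.6% | 6.3% | 7.6% | 11.5% |

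**Step 3: check by simulation.** The patient-level Mann-Whitney test was simulated under no treatment effect, with CTM-like scores capped at 100 and 4,000 runs per setting. At ICC 0.01, 0.02 and 0.05 the rejection rate was 10.2%, 14.9% and 28.3% with 4 teams, and 7.7%, 10.1% and 17.6% with 8. At ICC 0 it was 5.3% and 4.7%. The formula therefore describes the named test well, and the excess comes from clustering.

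**Step 4: outcomes from hospital data.** These do not depend on survey response. The protocol's accrual figures give 254 × 0.8 × 0.5 × 4 = 406 patients. With 4 teams, m = 101.6; at ICC 0.01, DE = 1 + 100.6 × 0.01 = 2.006 and the approximate error of a chi-square test is 16.6%.

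**Step 5: what a valid analysis delivers.** For a t-test on team means, the standard error of the difference is 19.6 × √(2 × DE / 95), with (teams − 2) degrees of freedom. Power for 7 points follows from the noncentral t distribution.
- 4 teams, ICC 0.01: SE = 19.6 × √(2 × 1.465 / 95) = 3.44; 2 degrees of freedom, critical value 4.30; power about 22%.
- 8 teams, ICC 0.01: DE = 1.2275; SE = 3.15; 6 degrees of freedom, critical value 2.45; power about 46%.
- Even at ICC 0, power is about 29% with 4 teams and 54% with 8, because of the few degrees of freedom.

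**The case against.** **The inflation is conditional.** At ICC exactly 0 there is none, and at ICC 0.001 the error is only 5.1% to 5.5%. This stands. The 28% figure is the corner of the table with the fewest teams and the largest ICC, and should not be quoted alone. But the protocol offers no reason to take the ICC as 0, and the direction is certain for any positive value.

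**The protocol does not literally say the tests are run on patients.** True, but n is counted in patients, readmission and ED visits are patient events, and no team summary is described. Patient-level testing is the plain reading.

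**Stronger readings that the protocol does not support.**
- A reader might infer from the Mann-Whitney test that the effect cannot be reported in CTM-3 points. It can: the Statistical Analysis section also summarizes results by means and standard deviations, so a difference in points can be given. A rank test on a bounded score is a defensible choice in itself. What is missing is an interval for that difference that respects the teams.
- A reader might infer that the analysis must adjust for all the patient characteristics collected. An unadjusted analysis is valid if it respects the unit of randomization. Length of stay and most responsible diagnosis may be set after allocation, so they are not clean baseline covariates.
- A reader might infer that any team effect is counted as a treatment effect. Only the chance imbalance of team effects between arms is.

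**Conclusion.** The stated analysis does not fit the stated design. If outcomes are correlated within teams, the named tests give p-values that are too small and the 5% level is exceeded. With 190 completers and ICC 0.01 to 0.05, the true error is about 10-28% with 4 teams in total, 8-18% with 8 and 6-12% with 16. At ICC 0.001 to 0.005 it is about 5-8% across these team numbers. The mismatch and the direction follow from the protocol; the size rests on the assumed number of teams and ICC and on equal team sizes. It must be corrected, because it affects the primary outcome and every between-arm comparison.

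**What to change.** Replace the sentence on tests in the Statistical Analysis section with an analysis by randomized team.

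- **CTM-3:** a t-test on team means with (teams minus 2) degrees of freedom, or a linear mixed model with a random team effect and Kenward-Roger degrees of freedom. Name one of them as primary. Report the mean difference in points with a 95% CI.
- **Binary outcomes:** compare team-level proportions in the same way. With very few teams, logistic mixed models and GEE are fragile even with small-sample correction.
- **Mann-Whitney, Fisher's exact and chi-square tests on patients:** keep for description only.
- **Adjustment, if wanted:** limit it to one or two true baseline variables such as age and sex.
- **Design inputs:** state the number of teams and an assumed ICC, and restate the power that this analysis delivers.

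The analysis change needs no new data beyond team membership, which the allocation already defines. It has a real cost: intervals widen and power falls clearly, to the levels in Step 5 of the working. If there are few teams, the restated power will probably show that the trial needs more teams or a revised target. With only one team per arm, no analysis could separate team from treatment.
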